Meanwhile, it is worth noting that there is still no effective strategy developed to assess the coagulation function of surgical patients on LOAPT. Given antiplatelet medication can have a significant impact on hemostasis and coagulation, the risk of intraoperative hemorrhage and postoperative intracranial bleeding (PIB) is a major focus because they can cause fatality [1, 2]. Though the preoperative screening of coagulation function could be effective in protecting patients from developing hemorrhagic complications, those commonly used methods are not applicable to assess the coagulation function of patients on LOAPT as the antiplatelet medication mainly affects platelet function, rather than clotting factors. Notably, there are various tools, such as thromboelastogram (TEG), reported to aid medical professionals in assessing the platelet function in the cardiac surgery and intracranial traumatic injury [17, 18]. Therefore, they have a potential to assist with the development of suitable treatment strategy for SSICH patients on LOAPT.

In addition to hemorrhagic complications, ischemic complications are also a problem worthy of consideration during the management of SSICH patients on LOAPT due to the hypercoagulable state caused by discontinuing antiplatelet medications. Besides, even though patients are stable after receiving appropriate treatment, it remains debatable to resume antiplatelet treatment. Therefore, there are many SSICH patients who have a history of antiplatelet treatment still stopping antiplatelet treatment after primary hemorrhage, which makes them under high risk of ischemic complications.

According to a previous study, the outcome after spontaneous intracerebral hemorrhage is poor, and the mortality could exceed 30% [1, 19]. Nevertheless, considering a lack of clarity on the effect and safety of emergency surgery for SSICH patients on LOAPT, there is no evidence gathered to support clinical decision-making. Therefore, a prospective cohort study will be conducted to investigate the safety and effect of emergency surgery for SSICH patients on LOAPT, based on which a scientific strategy will be proposed for the selection of an appropriate treatment.

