**Fig. 1 Fig1:**
[figure not shown]
Research flow chart

In order to achieve the research objective, it is necessary to recruit all SSICH patients except those not on LOAPT receiving conservative treatment. The inclusion and exclusion criteria are detailed in Tables 1 and 2, respectively. Three cohorts, including two comparative groups and one observational group (Fig. 1), will be established. Firstly, in order to measure the effect of emergency surgery, a comparison will be drawn of the outcomes and complications between SSICH patients on LOAPT receiving emergency surgery and those receiving conservative treatment. Secondly, in order to evaluate the safety of emergency surgery, hemorrhagic complications will be compared between operated SSICH patients who are on LOAPT and those not on LOAPT. Thirdly, the clinical characteristics and coagulation function of SSICH patients on LOAPT will be analyzed to assess the risk of developing ischemic diseases after discontinuing antiplatelet treatment, based on which an effective approach to the assessment of coagulation state will be established for surgery.

**Table 1 Tab1:** Inclusion criteria

Inclusion criteria: (1) 18–75 years old; (2) non-traumatic intracerebral hemorrhage; (3) severe intracerebral hemorrhage, which was defined as patients with supratentorial bleeding volume > 30 ml, infratentorial bleeding volume > 10 ml, midline shift > 1 cm, or large intraventricular hematoma; (4) Glasgow coma score (GCS) < 13; (5) family members agree to provide an informed written consent.

**Table 2 Tab2:** Exclusion criteria

Exclusion criteria: (1) patients had cerebrovascular diseases, e.g., intracranial aneurysm or vascular malformation, and intracranial tumors, which were associated with hemorrhage; (2) hemorrhagic transformation of cerebral infarction; (3) hemorrhage caused by venous thrombosis; (4) patients with severe coagulation disorder, e.g., hemophilia; (5) patients with coagulation dysfunction caused by malignant tumor, hypohepatia, renal dysfunction, thrombocytopenia, coagulation diseases, and so on; (6) patients receiving other anticoagulation medications (vitamin K antagonist and new oral anticoagulants); (7) patients not on LOAPT who receive conservative treatment; (8) the patients who died before or on arriving at the hospital and within a short period (6 h) after admission.	

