### Outcomes and study endpoints

All patients will be closely monitored until death or 6 months after the occurrence primary hemorrhage. In this study, the following outcomes will be taken into consideration (Table 3). The primary outcome is the total mortality, including in-hospital and out-of-hospital mortality. The second outcome is the postoperative hemorrhagic complication, and the PIB is our main focus. The functional outcome of patients is another outcome interesting us and will be assessed using modified Rankin scale (mRS). The postoperative adverse cardiovascular/cerebral events (ACCE) include the region of original stroke enlarging, new ischemic stroke occurring outside the operative region, myocardial infarction, repeated revascularization, and deep venous thrombus. The screening, evaluation, and follow-up schedules are detailed in Table 4.

**Table 3 Tab3:** Outcomes to be taken in consideration

(1) Total mortality; (2) postoperative hemorrhagic complication; (3) patients’ functional outcome; (4) postoperative adverse cardiovascular/cerebral events (ACCE).

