### Study definition

After admission, all of the patients would receive standardized care according to the guidelines. Severe spontaneous intracerebral hemorrhage (SSICH) is confirmed by both severe intracerebral hemorrhage radiologically and clinical coma (GCS < 13).

In definition, “on long-term oral antiplatelet therapy (on LOAPT)” refers to patients that received oral antiplatelet treatment on a continued basis for more than 7 days and discontinued antiplatelet medication no more than 7 days after the occurrence of hemorrhage. Antiplatelet therapy involved aspirin, clopidogrel, and dual antiplatelet treatment. Postoperative intracerebral bleeding (PIB) was defined as rehemorrhage within the operative region or new intracerebral hemorrhage associated with the operation on radiological examination.

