### Data collection

In case the patients meet our criteria, all information, including the demography, clinical information, preoperative radiological data, intraoperative findings, and laboratory and TEG data, will be recorded on the case report form (CRF). After being discharged, all the patients were followed up on a regular basis by outpatient visit and on telephone 3 months and 6 months after primary hemorrhage, respectively. During each follow-up visit, the survival condition, mRS, ACCE, and medication will be recorded. If the patients feel unable to undergo radiological examination in the participating center, a follow-up cranial image will be required. Once radiological examination is completed, the patients’ imaging data will be transmitted to the Tiantan hospital (this center will work as an imaging interpretation center) to reconfirm several events, including SSICH, PIB, and postoperative ischemic disease. During the study, the researchers are required to protect privacy for the patients and ensure the confidentiality of their medical information. The information collection schedule is presented in Table 4.

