## Results

China National Clinical Research Center for Neurological Diseases will be responsible for data analysis. Sample size was calculated by using PASS (Version 15, NCSS corporation, American). All sample size calculations were performed by conducting two-sided test, *α* = 0.05 and *β* = 80% (the degree of control = 80%). In this study, two comparison groups will be established, with the primary and secondary outcomes as the focus in this study. According to our unpublished data collected from 7 participating centers in 2019, for SSICH patients on LOAPT, the total mortality was about 30% for operated patients and 45% for the patients receiving conservative treatment, with the ratio of two groups reaching about 1:1.5. Moreover, for operated SSICH patients, the incidence of PIB was about 23% for patients on LOAPT and 10% for patient not on LOAPT, with the ratio of two groups reaching about 1:2.5. With regard to the primary outcome, our sample size was calculated as 196 (196 SSICH patients on LOAPT, operation group: *n* = 78; conservation group: *n* = 118). As for the secondary outcome, the sample size was 247 (247 operated SSICH patients, LOAPT group: *n* = 70; non-LOAPT group: *n* = 177). Moreover, in order to establish the coagulation function assessment system, the area under curve was expected to be 0.7, and the sample size was set to 92 (92 operated SSICH patients on LOAPT, PIB group: *n* = 23; non-PIB group: *n* = 69). In this case, a minimum of 387 SSICH patients (includes 118 patients on LOAPT receiving conservative treatment, 92 patients on LOAPT receiving emergency surgery, and 177 patients not on LOAPT receiving emergency surgery) may be required in this study to reach our research objective. Thus, to ensure final statistics, a total of 400 patients (patients on LOAPT receiving conservative treatment, *n* = 120; patients on LOAPT receiving emergency surgery, *n* = 100; patients not on LOAPT receiving emergency surgery, *n* = 180; Fig. 1) will be recruited. In this study, 10% of patients would be lost during follow-up. Finally, we decided to recruit 450 appropriate patients.

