All statistical analyses were conducted with the assistance of SPSS (Version 22.0, IBM, American). The data was indicated as mean (x) ± standard deviation (SD) for normally distributed data, median, and interquartile range (IQR) for skewed distributed data or number (*n*) and percentage (%). In this study, two main comparative groups and an observational cohort will be established, as shown in Fig. 1. Firstly, in order to investigate the effect of emergency neurosurgery, a comparison will be performed between SSICH patients on LOAPT receiving conservative treatment and those receiving emergency neurosurgery. Secondly, in order to investigate the safety of emergency neurosurgery, a comparison will be performed between operated SSICH patients on LOAPT and those not on LOAPT. Thirdly, in order to investigate the intra/postoperative complications and the risk of ischemic disease after discontinuing antiplatelet treatment, the characteristics of SSICH patients on LOAPT will be analyzed; moreover, because the history of previous neural ischemic events or cardiac events could affect the risk of postoperative ischemic events, we would perform the subgroup analysis depending on this history to further investigate the effect of discontinuing antiplatelet treatment on the risk of ischemic disease. The difference will be compared by conducting χ^2^ test, Mann-Whitney *U* tests, or Student’s *t* tests. The independent risk factors were analyzed by logistic regression, while the factors with *p* < 0.10 in univariate analysis were entered into a multivariate logistic regression model. The result was indicated as odd ratio (OR) and 95% confident interval (CI). The receiver operating characteristic (ROC) curve analysis was performed to test the prediction value of different parameters and different methods. An area under the curve (AUC) in a ROC analysis of ≥ 0.7 is considered as a clinical utility, while *p* value of < 0.05 was treated as statistically significant.

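### PIB is confirmed only by imaging, so a postoperative bleed found at re-operation, or a death before any postoperative scan, falls by default into the no-PIB group

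*Protocol article*

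**What the plan says.** Study definition gives PIB as "rehemorrhage within the operative region or new intracerebral hemorrhage associated with the operation on radiological examination". Data collection sends images to one interpretation centre "to reconfirm several events, including SSICH, PIB, and postoperative ischemic disease". The same section says that "preoperative radiological data, intraoperative findings, and laboratory and TEG data, will be recorded on the case report form". Intraoperative findings are therefore collected, but they are not part of the PIB definition.

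PIB carries much of the plan. Outcomes and study endpoints states: "The second outcome is the postoperative hemorrhagic complication, and the PIB is our main focus". The statistical text in Results says that "in order to investigate the safety of emergency neurosurgery, a comparison will be performed between operated SSICH patients on LOAPT and those not on LOAPT". PIB also sets the sample size for that comparison and is the outcome for the coagulation assessment system. The Background explains the interest: "the risk of intraoperative hemorrhage and postoperative intracranial bleeding (PIB) is a major focus because they can cause fatality".

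The article does not name findings at re-operation, autopsy or an adjudicated cause of death as a way to establish PIB.

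**The concern.** The endpoint is studied because it can kill, yet its definition depends on a scan that the worst-affected patients may not live to have. A re-bleed seen directly at re-operation also fails the definition if no scan came first. With a binary endpoint analysed by χ² test and logistic regression, a patient who does not meet the definition lands in the no-PIB group unless another rule says otherwise.

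Two analyses are exposed. In the safety comparison, missed bleeds reduce the observed PIB rates. If they are more frequent on LOAPT, the contrast is biased towards no difference. In the ROC analysis, severe bleeders would sit among the non-bleeders.

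The mortality endpoint does not close the gap. It is planned for surgery versus conservative treatment within LOAPT patients, not for operated patients on versus not on LOAPT.

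**Working it through.** **Inputs.** From Results: PIB 23% on LOAPT and 10% not on LOAPT; two-sided α 0.05; power 80%; ratio 1:2.5; stated size 70 + 177 = 247; planned operated patients 100 and 180; ROC sample 92, of whom 23 with PIB; expected AUC 0.7. The share of bleeds never imaged is not given. Shares of 0% to 30% are assumed below.

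**The plan's own figure.** The pooled two-proportion formula at 23% versus 10%, 1:2.5, two-sided 0.05 and 80% power gives 84 + 210 = 294, not 247. That mismatch is a separate matter and neither supports nor weakens this point. Power at 70/177 is 74%. The illustration uses the planned 100/180.

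**Formulas.** Observed rate = true rate × (1 − missed share). Power = Φ[(|p1 − p2| − 1.96·SE0)/SE1], where SE0 = √[p̄(1 − p̄)(1/n1 + 1/n2)] and SE1 = √[p1(1 − p1)/n1 + p2(1 − p2)/n2].

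- None missed: p̄ = (23 + 18)/280 = 0.1464; SE0 = 0.0441; SE1 = 0.0477; (0.13 − 0.0864)/0.0477 = 0.914; power 82%.
- 10% missed in both groups: rates 0.207 and 0.090; p̄ = 36.9/280 = 0.1318; SE0 = 0.0422; SE1 = 0.0458; (0.117 − 0.0827)/0.0458 = 0.749; power 77%.

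| Missed, LOAPT / non-LOAPT (assumed) | Observed PIB | Difference (points) | Risk ratio | Odds ratio | Power at 100/180 |
|---|---|---|---|---|---|
| 0 / 0 | 23.0% v 10.0% | 13.0 | 2.30 | 2.69 | 82% |
| 10% / 10% | 20.7% v 9.0% | 11.7 | 2.30 | 2.64 | 77% |
| 20% / 20% | 18.4% v 8.0% | 10.4 | 2.30 | 2.59 | 72% |
| 20% / 10% | 18.4% v 9.0% | 9.4 | 2.04 | 2.28 | 62% |
| 30% / 15% | 16.1% v 8.5% | 7.6 | 1.89 | 2.07 | 49% |

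Odds ratio = [p1/(1 − p1)] / [p2/(1 − p2)].

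The table separates two cases. Equal loss costs power and shrinks the difference, but leaves the risk ratio unchanged and barely moves the odds ratio, the measure the plan reports. Unequal loss is needed to distort the ratio.

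**ROC analysis.** Of 23 planned PIB cases, 10% is 2.3. If 2 move to the non-PIB group, it holds 69 + 2 = 71. If those 2 resemble the other bleeders, the expected AUC becomes (69/71) × 0.7 + (2/71) × 0.5 = 0.694. The shift is small, but the planned AUC lies exactly on the plan's 0.7 threshold for clinical utility. If the missed bleeders have the most abnormal platelet function, the shift would be larger.

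**The case against.** The strongest case against is that the problem is largely inferred. A reader might conclude that the plan scores unscanned deaths as bleed-free and so misses the most lethal form of the harm. The documents do not support that. No written rule classifies an operated patient without a postoperative scan, and a fatal bleed that was scanned does count. Falling into the no-PIB group is the default of a binary definition, not an instruction in the text.

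Nor does the roughly 30% mortality expected in operated LOAPT patients show that unscanned deaths are common. It is total mortality, in and out of hospital, with follow-up to 6 months. Deaths within 6 hours of admission are excluded altogether. Table 4 may schedule an early scan, which would leave few patients at risk, although it could not image those who die or are re-operated before it.

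The wording also leaves room. The radiological condition could attach only to the second half of the definition, though central reconfirmation from images favours reading it across both. The second outcome is the wider postoperative hemorrhagic complication, under which a bleed found at re-operation might fall, but no criteria for it are given.

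Finally, the 23% and 10% come from the centres' own 2019 data and may already be imaging-based. If so, the planning rates include the undercount and the power loss disappears, while the undercount itself remains. An imaging-based, centrally read endpoint is objective, which is valuable in a non-randomised study and worth keeping.

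These points limit the size and wording of the concern. They do not supply another route to the event.

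**Conclusion.** The point holds in a limited form. As defined, PIB needs a radiological examination, so bleeds found only at re-operation, and any bleed in a patient who dies before a postoperative scan, have no stated way to be counted. They would by default join the no-PIB group.

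How many patients this affects cannot be derived from the article. The power figures are illustrations: they rest on assumed missed shares and on treating 23% and 10% as true rates. The statement that surgery on LOAPT would look safer on the ratio scale requires a larger missed share on LOAPT, which is plausible but which nothing in the article establishes. This is a worthwhile, inexpensive improvement to a stated endpoint definition, not evidence that the safety comparison fails.

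**What to change.** Four changes, all to outcome classification and none to patient care:

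1. Define PIB as confirmed by imaging or by findings at re-operation.
2. Report, by group, the number of operated patients who die without a postoperative scan.
3. Do not place those patients in the non-PIB group of the ROC analysis.
4. Pre-state a sensitivity analysis of the LOAPT versus non-LOAPT comparison using PIB or death before the first postoperative scan.

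**Cost.** One sentence in the definition, one count and one extra analysis. The composite includes some deaths not due to bleeding. It therefore gives an upper limit for unscanned deaths within each group and should stand beside the imaging-based endpoint, not replace it. The article's list of CRF items does not name postoperative scan dates or re-operations. If the CRF lacks them, they must be taken from the central imaging and operative records.

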### Thrombelastography (TEG) test and coagulation function assessment system

TEG is performed to monitor the function of platelet with the assistance of Thrombelastograph Coagulation Analyzer (TEG model 5000, Haemoscope Corporation, Niles IL, American). All parameters, including maximum amplitude (MA, mm), citric acid kaolin tracing (CK), reptilase tracing (A), aspirin tracing (AA), and clopidogrel tracing (ADP), are recorded through standard tracing. Based on MA, the rate of platelet inhibition was calculated using the formula as shown below:
$$ AA/ ADP\%=\frac{\mathrm{MA}\left(\mathrm{CK}\right)-\mathrm{MA}\left(\mathrm{A}\mathrm{A}/\mathrm{ADP}\right)}{\Big(\mathrm{MA}\left(\mathrm{CK}\right)-\mathrm{MA}\left(\mathrm{A}\right)} $$

where AA% represents the inhibition to platelet caused by aspirin, and ADP% indicates the inhibition to platelet caused by clopidogrel. Further with traditional coagulation test including bleeding time, prothrombin time, activated partial thromboplastin time, and fibrinogen as well as TEG, we plan to establish a combined coagulation function assessment system in order to assess the surgical risk facing SSICH patients on LOAPT, with the focus placed on PIB. Moreover, for the patients not on LOAPT, it is considered that these patients have normal platelet function and do not need to undergo further relative test.

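### The ROC objective is sized and described on one pooled LOAPT group although AA% and ADP% each reflect one drug, and no drug-matched analysis is named

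*Protocol article*

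**What the plan says.** All places are in the protocol article.

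- **Study definition:** one LOAPT category covers three regimens: "Antiplatelet therapy involved aspirin, clopidogrel, and dual antiplatelet treatment". No split is given.
- **Thrombelastography section:** the inhibition values are drug-specific: "AA% represents the inhibition to platelet caused by aspirin, and ADP% indicates the inhibition to platelet caused by clopidogrel". Recording is not limited by drug: "All parameters, including maximum amplitude (MA, mm), citric acid kaolin tracing (CK), reptilase tracing (A), aspirin tracing (AA), and clopidogrel tracing (ADP), are recorded". The goal is wider than single values: "we plan to establish a combined coagulation function assessment system in order to assess the surgical risk facing SSICH patients on LOAPT", drawing on TEG and the traditional clotting tests, with PIB as the focus.
- **Results, sample size paragraph:** "the area under curve was expected to be 0.7, and the sample size was set to 92", made up of 23 patients with PIB and 69 without, all operated and on LOAPT.
- **Results, analysis paragraph:** "The receiver operating characteristic (ROC) curve analysis was performed to test the prediction value of different parameters and different methods". The pass mark follows: "An area under the curve (AUC) in a ROC analysis of ≥ 0.7 is considered as a clinical utility". Logistic regression takes in factors with univariate p < 0.10. The only subgroup analysis named is by history of ischaemic or cardiac events.

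**The concern.** AA% in a patient on clopidogrel alone carries no aspirin signal, and ADP% in a patient on aspirin alone carries no clopidogrel signal. A strongly inhibited patient can therefore rank as low risk on the channel that does not match the drug. If a single value is run through a ROC curve over the whole LOAPT group, its AUC moves toward 0.5.

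The pass mark is a fixed 0.7 and the AUC assumed for planning is also 0.7, so there is no room for such dilution. A value that works in the patients it is meant for could be reported as lacking clinical utility, and any cut-off derived would depend on this cohort's drug mix. The coagulation assessment method is one of the four aims listed under Study design.

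**Working it through.** **1. The plan's own figure.** Inputs from Results: AUC 0.7, two-sided α 0.05, power 80%, 23 + 69. The null AUC is not stated; 0.5 is assumed. The Hanley-McNeil variance at AUC 0.5 is (m + n + 1)/(12mn).
- m = 23, n = 69: 93/19,044 = 0.00488, SE 0.0699. Power = Φ(0.2/0.0699 − 1.96) = 0.82.
- m = 22, n = 66: SE 0.0715, power 0.799, just short.

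So 23 + 69 = 92 is reproduced exactly, as a one-sample AUC test in a single undivided group.

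**2. Dilution of a single value.** Let p be the share taking the drug that the value measures and A the AUC within them. Assume that takers and non-takers have the same mean value and the same PIB rate. Pairs of two takers contribute A, pairs of two non-takers 0.5, and mixed pairs about halfway:

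pooled AUC ≈ p²A + 2p(1 − p)[0.5 + (A − 0.5)/2] + (1 − p)²(0.5) = 0.5 + p(A − 0.5)

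| A | p = 0.8 | p = 0.6 | p = 0.4 |
|---|---|---|---|
| 0.75 | 0.70 | 0.65 | 0.60 |
| 0.80 | 0.74 | 0.68 | 0.62 |

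If takers' values are 1 to 2 SD higher, the pooled AUC is lower still: A = 0.80 and p = 0.6 give 0.65 to 0.62. To keep the pooled AUC at 0.7, about 80 to 88% must take the matching drug when A = 0.75, and 67 to 80% when A = 0.80.

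**3. Simulation with three regimens** (400,000 patients per setting). Assumptions: PIB 23% (Results); channel values normal with SD 1; on-drug mean shift 0 or 2 SD; logit of PIB = constant + 1.0 × inhibition on the drug taken, using the higher value for dual patients. Ranges span the two shifts.

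| Aspirin/clopidogrel/dual (assumed) | Drug-matched | AA% | ADP% | Main-effects logistic, AA% + ADP% |
|---|---|---|---|---|
| 60/25/15 | 0.74 | 0.64–0.66 | 0.56–0.58 | 0.68 |
| 40/40/20 | 0.74 | 0.60–0.62 | 0.60–0.62 | 0.67 |
| 80/10/10 | 0.74 | 0.69–0.70 | 0.53–0.54 | 0.70–0.71 |

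If off-drug values vary little (SD 0.3 instead of 1), the main-effects model reaches 0.71 to 0.73 in all three mixes.

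**4. Effect on the 0.7 criterion.** With 23/69 and the Hanley-McNeil SE, the chance that the observed AUC reaches 0.7 is Φ((AUC − 0.7)/SE):
- true AUC 0.75: Φ(0.05/0.0639) = 78%
- 0.65: Φ(−0.05/0.0693) = 24%
- 0.60: Φ(−0.10/0.0704) = 8%

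**5. Restricting to takers within the 92.** Power for AUC 0.7 against 0.5 = Φ((0.2 − 1.96·SE₀)/SE₁), with SE₀ at AUC 0.5 and SE₁ at AUC 0.7. This version gives 83% at 23/69.

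| Share on matching drug | PIB / non-PIB | Power | Operated LOAPT patients needed for 92 takers |
|---|---|---|---|
| 80% | 18 / 55 | 73% | 92/0.8 = 115 |
| 60% | 14 / 41 | 61% | 92/0.6 → 154 |
| 40% | 9 / 28 | 43% | 92/0.4 = 230 |

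**The case against.** **The article does not say that each value is tested in every patient.** A reader might infer this from the pooled 92 and the unrestricted recording of tracings, but the text names no analysis set for any parameter. Recording a tracing is not the same as analysing it in everyone, and labelling the values by drug is compatible with reading each by drug. This stands: the document does not support the claim that a wrong analysis was expressly specified. It does not remove the point. The article already fixes the sample, the method and the pass mark, and does so for one undivided group. If drug-matched sets were intended, the 92 does not give 80% power for them.

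**The stated goal is a combined system.** A low AUC for one channel would not by itself defeat the fourth aim, and main effects do repair part of the loss. This also stands. The repair is incomplete in two of the three assumed mixes when off-drug values vary as much as on-drug values, and nearly complete when they vary little.

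**Regimen is not excluded from the logistic model.** Correct: no candidate factors are listed. A regimen main effect, however, does not make the weight of AA% or ADP% depend on the drug taken.

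**Dilution is neither certain nor always large.** With 80% on aspirin alone and 10% dual, AA% stays at 0.69 to 0.70. If takers of the drug are over-represented among PIB cases (assumed 80% of PIB and 60% of non-PIB patients), a within-drug AUC of 0.75 pools to 0.70 to 0.72. Part of that AUC would then reflect which drug was taken rather than the degree of inhibition.

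**Details may sit in a document not shown.** Possible, and a reason to word this as a change to make rather than as an error in the trial.

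**Conclusion.** The point holds in a limited form. The article pools three regimens, defines each inhibition value for one drug, sizes and describes the ROC objective on one group of 92, and names no drug-matched analysis. Followed as written, AA% or ADP% used singly loses discrimination: from 0.74 to about 0.64–0.66 and 0.56–0.58 under an assumed 60/25/15 mix. A main-effects combination recovers part of this, reaching about 0.67 to 0.73 depending on the mix and on off-drug variability.

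These sizes rest on an assumed drug mix, normal channel values, risk driven by inhibition on the drug taken, and a null AUC of 0.5. The direction is firm unless PIB is concentrated in takers of one drug. The figures do not show that the sample size of 92 is miscalculated, since it reproduces, or that the assessment aim will fail. It is worth correcting because the remedy costs almost nothing.

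**What to change.** 1. Assess AA% alone only in patients taking aspirin (alone or dual) and ADP% alone only in patients taking clopidogrel (alone or dual).
2. For the pooled ROC and logistic analyses, prespecify a drug-matched inhibition value: AA% for aspirin only, ADP% for clopidogrel only, and a stated rule for dual treatment, such as the higher of the two. The alternative is to enter AA% and ADP% with drug-by-value terms; with 23 expected events, the single matched value is more economical. Base the rule on the drug actually taken: the higher value taken regardless of regimen gave 0.74 with a 2 SD on-drug shift but only 0.67 to 0.68 with no shift.
3. Include regimen (single or dual) in the model, and report PIB by regimen with 95% CI beside the pooled LOAPT rate.
4. State that the 92 applies to the pooled drug-matched or combined score, and that single-channel power is lower: about 73%, 61% or 43% if 80%, 60% or 40% take the matching drug.

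Cost: analysis wording only. Both tracings are already recorded, and the matched value needs only each patient's antiplatelet drug at admission. The price is that single-channel ROC results rest on fewer than 92 patients; the matched value keeps all of them.

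### The bleeding comparison defines its controls only as everyone outside the LOAPT definition, so operated patients with short or intermittent antiplatelet use count as controls with normal platelet function

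*Protocol article*

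**What the plan says.** The Study definition section gives a positive definition for one exposure group only. A patient is on LOAPT if they "received oral antiplatelet treatment on a continued basis for more than 7 days". A second condition in the same sentence concerns the stop date, namely that the patient "discontinued antiplatelet medication no more than 7 days after the occurrence of hemorrhage". The next sentence adds: "Antiplatelet therapy involved aspirin, clopidogrel, and dual antiplatelet treatment". There is no matching definition of a patient not on LOAPT.

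The Study design section sets the recruitment rule: "it is necessary to recruit all SSICH patients except those not on LOAPT receiving conservative treatment". For safety, the same section says that "hemorrhagic complications will be compared between operated SSICH patients who are on LOAPT and those not on LOAPT".

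The only drug-related exclusion in Table 2 is for "patients receiving other anticoagulation medications (vitamin K antagonist and new oral anticoagulants". Its other coagulation exclusions concern disorders caused by disease.

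The section on TEG and the coagulation assessment system says of the control group: "for the patients not on LOAPT, it is considered that these patients have normal platelet function and do not need to undergo further relative test".

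The sample size paragraph under Results gives the expected rates: "the incidence of PIB was about 23% for patients on LOAPT and 10% for patient not on LOAPT".

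**The concern.** The safety question is whether antiplatelet exposure raises bleeding after emergency surgery. It needs a comparator without antiplatelet effect. As written, the comparator is whatever remains once LOAPT patients are removed, and that remainder includes patients with some recent exposure. The TEG section nevertheless asserts that the whole group has normal platelet function and waives platelet testing in it.

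If exposed patients bleed more, as the plan expects, counting them as controls raises the control rate and shrinks the observed excess. The error runs toward the conclusion that operating on LOAPT patients is about as safe as operating on others. For a study meant to inform whether to operate, that is the less cautious direction.

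**Working it through.** **Step 1. Who becomes a control.** Apply the rules in order to an operated patient who otherwise meets Tables 1 and 2.

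- Antiplatelet treatment for 5 days before the bleed: fails the more-than-7-days clause, so not on LOAPT.
- Intermittent use: fails the continued-basis clause, so not on LOAPT.
- Table 2, criterion 6 names vitamin K antagonists and new oral anticoagulants, so neither patient is excluded.
- Table 2, criteria 4 and 5 list diseases (haemophilia, malignancy, liver or renal dysfunction, thrombocytopenia and similar), so neither patient is excluded.
- Table 2, criterion 7 removes non-LOAPT patients only if treated conservatively. Both were operated, so both are recruited as controls.

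**Step 2. Does normal platelet function follow?** No. The definition sets a duration and continuity threshold, and failing it does not mean being unexposed. The Background itself says that antiplatelet drugs act mainly on platelet function and that the commonly used coagulation tests are not suited to assessing it.

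**Step 3. The plan's own figure.** The protocol gives 247 operated patients (70 + 177) for PIB, from 23% against 10%, a ratio of 1:2.5, two-sided 0.05 and 80% power. The usual pooled two-proportion formula, with k = 2.5 and mean rate (0.23 + 2.5 × 0.10)/3.5 = 0.1371, is

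n = [1.960 × √(1.4 × 0.1371 × 0.8629) + 0.842 × √(0.23 × 0.77 + 0.10 × 0.90/2.5)]² / 0.13²

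This is (0.798 + 0.389)²/0.0169, which rounds up to 84. The total is 84 + 210 = 294, so 247 is not reproduced. That is a separate matter: the present point rests on the definition and uses only the two rates.

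**Step 4. Dilution if the 10% applies to unexposed patients.** Let f be the share of controls with antiplatelet exposure and g the fraction of the 13-point excess risk they carry. The documents give neither, so the values below are assumptions.

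Control rate = 0.10 + 0.13 × f × g; difference = 0.13 × (1 − f × g).

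| f | g | Control rate | Difference |
|---|---|---|---|
| 0 | any | 10.0% | 13.0 points |
| 5% | 1 | 10.65% | 12.35 points |
| 10% | 1 | 11.3% | 11.7 points |
| 10% | 0.5 | 10.65% | 12.35 points |

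**Step 5. Dilution if the 10% already contains such patients.** With g = 1, the unexposed rate is (0.10 − 0.23f)/(1 − f), and the difference from unexposed patients is 0.13/(1 − f).

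- f = 5%: unexposed rate 0.0885/0.95 = 9.3%; difference 13.7 points.
- f = 10%: unexposed rate 0.077/0.90 = 8.6%; difference 14.4 points.

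The study would still estimate 13 points, so planned power is untouched, but 13 understates the contrast with unexposed patients. The direction is the same in both steps.

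**The case against.** Four points on the other side deserve weight.

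- **Other agents.** A reader might infer that long-term users of an antiplatelet drug other than aspirin or clopidogrel also fall among the controls. The text does not establish this. The operative sentence covers oral antiplatelet treatment without naming a drug, and the sentence that names drugs says only what the therapy involved, which may be illustrative. The classification is unclear and should be stated, but it cannot be counted as a known misclassification.
- **Visibility.** A reader might also infer that exposed controls would be undetectable because testing is waived. That goes too far. Drug, duration and stop date must be asked of every patient in order to apply the LOAPT definition, and the Data collection section puts clinical information on the case report form. The waiver covers platelet testing, not medication history.
- **Power.** With 100 against 180 patients, power is 82.0% at 23% against 10%, and would be 77.4% or 72.3% with 5% or 10% of controls exposed at full risk. It is tempting to report this as a loss. But the 10% is described as the rate seen at the same seven centres in patients not on LOAPT. If the same rule was used there, the mixture is already inside it and the planned power does not fall. The loss also assumes that someone a few days into treatment, or using it intermittently, carries the full LOAPT risk, which nothing in the article supports.
- **Condensed article.** Fig. 1 and Table 4 are not shown, and a fuller protocol may deal with borderline exposure. That is fair as far as missing detail goes. It does not remove the point, because the article positively states both the recruitment rule and the claim of normal platelet function, and the second does not follow from the definition.

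The phrase at the end of Table 2, criterion 5 that leaves its list open does not help either: its listed causes are diseases, not drugs.

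**Conclusion.** The point holds for duration and continuity of use. Followed as written, the rules place operated patients with 7 days or less of antiplatelet use, or intermittent use, in the control group and treat them as having normal platelet function. Given the plan's premise that exposure raises PIB, the safety comparison is biased toward no excess bleeding.

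The direction follows from the plan; the size does not. With 5% to 10% of controls exposed at the full 23% risk, the difference moves by 0.65 to 1.3 points from 13 if the 10% is a rate in unexposed patients. It would be smaller with fewer such patients or lower risk, and could be negligible. No loss of planned power can be asserted. The case for change is that the comparator is wrongly specified and cheap to correct, not that a large bias has been shown.

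**What to change.** - Define controls positively: operated patients with no antiplatelet drug of any kind within a stated period before the haemorrhage, taken from the medication history already needed to classify LOAPT.
- Put operated patients with recent antiplatelet use that does not meet the LOAPT definition into a separate descriptive group. Alternatively, exclude them from the PIB comparison and include them in a sensitivity analysis.
- State whether the named drugs are the full list or examples, so that users of other oral antiplatelet agents are classified unambiguously.
- Limit the normal-platelet-function statement to controls who meet the new definition.

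The cost is one definition and one case report form field, with no new test. Some controls are lost from the largest group. At the assumed 5% to 10% this is 9 to 18 of the planned 180, leaving 171 to 162. That is below the protocol's calculated 177, so they should be replaced during recruitment.
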